## Recruitment manoeuvres (RM)

Patients enrolled in this study will undergo RMs. The RMs are only carried out by senior medical staff or senior trainees familiar with this technique. RM_Max_ and PUMPs are for participants randomised to the MBV protocol arm only. Patients assigned to the SPV arm may undergo a staircase RM (SRM) at the discretion of the treating clinician according to standard practice. (see “Standard practice staircase recruitment manoeuvre”).

All RMs will be performed in SIMV pressure controlled (PC) ventilation mode. The peak inspiratory pressure (Pi) is set to achieve a V_T_ of 6–8 ml/kg IBW. Preferably, V_T_ should result in DP ≤ 15 cmH_2_O above PEEP.

Before and after each RM, ABGs (pH, PaCO_2_, PaO_2_, HCO_3_), SpO_2_, end-tidal CO_2_ partial pressure (ETCO_2_), FiO_2_, PEEP, RR), and V_T_ will be recorded. In addition, during the RM_max_ (model-based ventilation arm) or (standard practice ventilation (SRM) arm, at each PEEP increment, Heart rate, rhythm, mean arterial pressure (MAP), SpO_2_, FiO_2_, V_T_, RR, ETCO_2_ and rates of use of vasoactive drugs will be recorded. This data will be valuable in assessing the safety of the RM_Max_, PUMP and SRM.

In many cases, where the lung stiffness, or respiratory elastance (E) is high, it will not be possible to deliver a V_T_ of 6 ml/kg IBW. Furthermore, during the RM, the delivered V_T_ may fall further as the elastance increases. As a result, it may be necessary to increase the respiratory rate to accommodate the reduction in minute ventilation. For example, if E is > 40 cmH_2_O/L (or compliance < 25 ml/cmH_2_O) in a patient weighing 58 kg (IBW), (normal range 15–20 cmH_2_O/L), the V_T_ will be < 6 ml/kg (< 350 ml) when the driving pressure is 15 cmH_2_O.

It is important that oxygenation targets in both arms are carefully followed to ensure a fair comparison between them. The SpO_2_ will be kept in the target range prior to any RM. This approach allows small decreases in oxygenation to be detected during the decremental PEEP phase of the recruitment manoeuvre, while also providing a sufficient buffer in the event of significant de-saturation due to ventilation perfusion (V/Q) mismatch. V/Q mismatch increases with higher airway pressures when pulmonary arterial blood is shunted away from the pulmonary capillaries by-passing aerated regions of the lung.

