### RM_Max_; MBV

The RM_Max_ is a computer-guided staircase RM procedure in the MBV intervention arm. This method is designed to safely increase the inspiratory pressure to a maximum airway pressure of 40–43 cmH_2_O, with DP limited to 15 cmH_2_O, and maximum PEEP limited to 25–28 cmH_2_O. The RM_Max_ is guided by the CURE software using a validated model-based method, which estimates elastance to determine the optimal PEEP [23, 31].

The RM_Max_ is carried out by intensive care specialists or senior trainees familiar with this technique. This procedure is only carried out during working hours (0800–1800 hours), but preferably within 4–6 h of enrolment. However, for patients enrolled overnight, unless there are compelling reasons to carry out an RM_Max_, this procedure may be delayed till the following morning (0800 hours).

Contra-indicated preconditions to an RM_Max_ are excluded using the RM checklist. If it is safe to proceed, the patient is prepared for the RM_Max_.

The following instructions are given to the clinician:

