Adjust oxygenation to meet the target range.Titrate sedation so the patient is not verbally responsive and has loss of their eyelash reflex. Use fentanyl or morphine increments with propofol to provide a “balanced” deeper sedation level. Give rocuronium 1.0–1.5 mg/kg through a reliable i.v. line; ensure the line is flushed.Set the ventilator to SIMV-PC (pressure control) mode.Set peak inspiratory pressure (Pi) to 15 cmH_2_O above PEEP.Ensure the initial PEEP is ≤ 15 cmH_2_O.Start maximum recruitment on the CURE soft programme.Follow the steps of the CURE soft protocol: during the RM_Max_, increase PEEP in steps of 4 cmH_2_O above the baseline PEEP level until Pi reaches 40–43 cmH_2_O or PEEP 25–28 cmH_2_O. Then reduce PEEP in 4 cmH_2_O decrements until the original starting PEEP is reached. Adjust FiO_2_ throughout the procedure to keep SpO_2_ ≥ 90%.Once PEEP has been returned to the initial setting, perform a second RM_max_ using the same method in point 7. The RM_Max_ is carried out twice. During the first RM_Max_ the elastance changes in PEEP level are more variable and therefore less predictable. The non-recruited lung is highly heterogeneous with regions of collapse and consolidation. The first RM_Max_ is used to recruit these de-recruited regions. The second manoeuvre is used to estimate optimal PEEP from repeated estimates of elastance changes during decremental PEEP titration.The CURE soft programme will recommend an optimal PEEP at the end of the second RM_Max_. You may either accept this computerised recommendation, or reject it (with a reason) if you feel the new PEEP level is inappropriate. If rejected, record your reason(s) on the programme.Return the patient to the previous ventilation mode.Adjust V_T_ to ≤ 6–8 ml/kg IBW. If the plateau pressure is > 30 cmH_2_O, adjust the V_T_ down to 4–6 ml/kg IBW and tolerate permissive hypercapnia. Also ensure that the DP remains at ≤ 15 cmH_2_O. You may increase the respiratory rate up to 30 breaths/min provided there is no significant auto-PEEP causing breath stacking.Reduce the ETT cuff pressure to the previous level and re-set ventilator alarms to previous settings.Record ABGs 30–60 mins after conclusion of the procedure.

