### PUMP: PEEP adjustment and monitoring procedure

PUMP is a regular mini-recruitment manoeuvre procedure designed to adjust PEEP based on patient-specific changes in condition. This mini-RM is also guided by CURE software and moves between ±4 cmH_2_O from the current PEEP. PUMP should be performed twice daily during normal working hours (0800–1800 hours) or at any other time if lung de-recruitment is considered to be the likely cause of new desaturation. The Pi will be left the same as in the current ventilator settings. To ensure a PUMP can be safely carried out, the RM checklist and preparation steps are to be followed. If the checklist preconditions are met, the PUMP may be carried out.

The following instructions are given to the clinician:
Titrate sedation so the patient is not verbally responsive and has loss of their eyelash reflex. Use fentanyl or morphine increments with propofol to provide a “balanced” deeper sedation level. Give rocuronium 0.5–1.0 mg/kg through a reliable i.v. line; ensure the line is flushed.Set the ventilator to SIMV-PC mode with the appropriate aforementioned settings.Reduce the PEEP to 4 cmH_2_O less than the current PEEP setting. The CURE software cannot estimate an optimal PEEP that is lower than the current PEEP setting.Start PUMP on the CURE soft programme.Follow the steps of the CURE soft PUMP protocol. During the PUMP procedure, increase PEEP in two steps of 4 cmH_2_O. Then decrease PEEP in two steps of 4 cmH_2_O (you may need to adjust the FiO_2_ to keep the SpO_2_ ≥ 90%).Once you have returned PEEP to the starting PEEP level (initial PEEP − 4 cmH_2_O), perform a second PUMP using the same method described in point 5.The CURE soft programme will recommend a new PEEP at the end of the second PUMP. You may either accept this computerised recommendation, or reject it (with a reason) if you feel the new PEEP level is inappropriate. If rejected, record your reason(s) on the programme.Return the patient to the previous ventilation mode.Adjust to V_T_ ≤ 6–8 ml/kg IBW. If the plateau pressure is > 30 cmH_2_O, adjust the V_T_ down to 4–6 ml/kg IBW and tolerate permissive hypercapnia. Also ensure that the DP remains ≤15 cmH_2_O. You may increase the respiratory rate up to 30 breaths/min provided there is no significant auto-PEEP causing breath stacking.Reduce the ETT cuff pressure to the previous level and re-set ventilator alarms to previous settings.Take an ABG 30 to 60 mins following the conclusion of the procedure

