Titrate sedation so the patient is not verbally responsive and has loss of their eyelash reflex. Use fentanyl or morphine increments with propofol to provide a “balanced” deeper sedation level. Give rocuronium 1.0–1.5 mg/kg through a reliable i.v. line; ensure the line is flushed.Set the ventilator to SIMV-PC mode.Set Pi to 15 cmH_2_O above PEEP.Ensure the initial PEEP is ≤ 15 cmH_2_O. If PEEP is set at ≤ 15 cmH_2_O, the corresponding plateau pressure will not exceed 30 cmH_2_O.Increase PEEP in a stepwise manner every minute in steps of 4 cmH_2_O to a achieve Pi of 40–43 cmH_2_O.Reduce PEEP to 24, and then by decrements of 2 cmH_2_O, every 2 min, until the SpO_2_ begins to fall by no less than 2% of the maximum observed. Hold PEEP at this level and then increase PEEP to the maximum that was previously used for 1 min before returning to a PEEP level 2 cmH_2_O above the level when the SpO_2_ was first noted to have fallen (the decrements in 2 cmH_2_O will allow a PEEP selection between 16 and 24 cmH_2_O, which is within the high PEEP protocol from the ARDS Clinical Network study of high versus low PEEP [4].If there is no desaturation during the decremental phase of the SRM, reduce PEEP to 16 cmH_2_O; no further changes in PEEP are required.Return the patient to the previous ventilation mode.Adjust the DP to ≤ 15 cmH_2_O to give a V_T_ ≤ 6–8 ml/kg IBW. If the plateau pressure is > 30 cmH_2_O, adjust the DP so that V_T_ is to 4–6 ml/kg IBW and tolerate permissive hypercapnia. You may increase the respiratory rate up to 30 breaths/min provided there is no significant auto-PEEP causing breath stacking.Reduce the ETT cuff pressure to the previous level and re-set ventilator alarms to previous settings. Record ABGs 30–60 mins after the conclusion of the procedure.

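### Two rules set inspiratory pressure during recruitment manoeuvres, and in less stiff lungs the bedside rule exceeds the protocol's own 8 ml/kg tidal volume

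*Protocol article*

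**What the plan says.** The section *Recruitment manoeuvres (RM)* of the protocol article gives a general rule for every manoeuvre: "The peak inspiratory pressure (Pi) is set to achieve a V_T_ of 6–8 ml/kg IBW". The next sentence brings in driving pressure as a preferred upper value: "Preferably, V_T_ should result in DP ≤ 15 cmH_2_O above PEEP". The description of RM_Max treats the same figure as a limit: "with DP limited to 15 cmH_2_O, and maximum PEEP limited to 25–28 cmH_2_O".

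The instructions to the clinician read differently. For RM_Max (section *RM_Max; MBV*) the step is "Set peak inspiratory pressure (Pi) to 15 cmH_2_O above PEEP". For the control arm's staircase manoeuvre (section *Standard practice SRM*) it is "Set Pi to 15 cmH_2_O above PEEP". Neither list sets a tidal-volume condition while the manoeuvre is running; both bring tidal volume back to the 6–8 ml/kg range once the patient is on the earlier ventilation mode again. The PEEP adjustment procedure (PUMP) has a third wording: "The Pi will be left the same as in the current ventilator settings".

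Two other places matter. *Tidal volumes (V_T) and driving pressures (DP) during MV* sets 6–8 ml/kg ideal body weight (IBW), caps driving pressure at 15 cmH2O, and permits volumes down to 4 ml/kg when needed. *Recruitment manoeuvres (RM)* acknowledges that 6 ml/kg will often be out of reach in stiff lungs.

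**The concern.** The general rule fixes the volume and lets the pressure follow. The bedside step fixes the pressure and lets the volume follow. In a patient whose lungs are not very stiff, the two give different manoeuvres, and the bedside step takes tidal volume above the range the protocol states for all manoeuvres. The protocol discusses only the opposite case, in which the target volume cannot be reached.

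Three things are at stake.

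- **Delivery.** What is delivered depends on which section the clinician follows.
- **Adherence and safety data.** Tidal volume is recorded at each PEEP increment of RM_Max and SRM so that safety can be assessed. With two rules, a recorded volume above 8 ml/kg cannot be classed as on or off protocol.
- **Balance between arms.** RM_Max is part of the protocol for the intervention arm and its staircase is run twice, while SRM is at the clinician's discretion in the control arm. Any excess would therefore fall mainly on the intervention arm.

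**Working it through.** **Relation used.** Tidal volume = driving pressure / elastance (V_T = DP/E), divided by IBW for ml/kg. This assumes full pressure equilibration, no patient effort and no auto-PEEP. If equilibration is incomplete, the delivered volume is lower than calculated.

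**Step 1: the protocol's own example.** The case is "if E is > 40 cmH_2_O/L (or compliance < 25 ml/cmH_2_O) in a patient weighing 58 kg (IBW"), and the stated result is "the V_T_ will be < 6 ml/kg (< 350 ml) when the driving pressure is 15 cmH_2_O".

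- 6 ml/kg × 58 kg = 348 ml, which matches the stated 350 ml after rounding.
- 15 / 40 = 0.375 L = 375 ml, and 375 / 58 = 6.5 ml/kg. The compliance form agrees: 15 × 25 = 375 ml.
- Elastance at which the volume equals 6 ml/kg: 15 / 0.348 = 43.1 cmH2O/L.

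The example does not reproduce. The statement holds only above about 43 cmH2O/L, not from 40 upward. The difference is about 7% (375 against 350 ml).

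**Step 2: is the bedside step really a fixed 15?** The RM_Max end points are PEEP 25–28 and inspiratory pressure 40–43 cmH2O: 25 + 15 = 40 and 28 + 15 = 43. The SRM steps say that a PEEP of at most 15 keeps plateau pressure within 30: 15 + 15 = 30. Both fit 15 used as a set value.

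**Step 3: stiff side.** At 58 kg and E above 43.1, a driving pressure of 15 gives less than 6 ml/kg. The protocol accepts this in *Recruitment manoeuvres (RM)* and in the ventilation settings, so the sections are compatible there.

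**Step 4: less stiff side.** The fixed step exceeds 8 ml/kg when E < 15 / (0.008 × IBW). For 58 kg this is 15 / 0.464 = 32.3. With a driving pressure of 15, the volume is 750 ml at E = 20, 600 ml at E = 25 and 500 ml at E = 30.

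| IBW (kg) | 8 ml/kg passed below E of | ml/kg at E = 20 | at E = 25 | at E = 30 |
|---|---|---|---|---|
| 50 | 37.5 | 15.0 | 12.0 | 10.0 |
| 58 | 32.3 | 12.9 | 10.3 | 8.6 |
| 70 | 26.8 | 10.7 | 8.6 | 7.1 |
| 80 | 23.4 | 9.4 | 7.5 | 6.25 |

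Only 58 kg comes from the protocol; the other weights are illustrative. The elastances 20, 25 and 30 are assumptions. They run from the top of the normal range the protocol quotes (15–20) to below its stiff-lung example (above 40).

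**Step 5: the general rule in the same patient.** At 58 kg, 6–8 ml/kg is 348–464 ml. Reaching it needs a driving pressure of 0.348 × 25 = 8.7 to 0.464 × 25 = 11.6 cmH2O at E = 25, and 10.4 to 13.9 at E = 30. The bedside step sets 15 in both cases.

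**The case against.** The strongest reply is that the numbered steps agree with each other and with the pressure ceilings, so a clinician working down the list has one clear instruction, and only an introductory sentence disagrees. The manoeuvres are brief, are done by specialists or senior trainees, and are followed by readjustment of tidal volume. This stands as a limit on the consequences. It does not remove the contradiction, because the introductory sentence is the stated rule for every manoeuvre and the steps do not say that they replace it.

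Three stronger readings are tempting, and the document does not support them.

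- **That the rules agree only in a narrow band of elastance.** A reader might infer an upper limit as well, about 43 cmH2O/L at 58 kg. But the protocol caps driving pressure at 15 and accepts lower volumes in stiff lungs, so both wordings lead to the same setting there. The conflict is one-sided.
- **That every patient given RM_Max receives more than 8 ml/kg.** Only those below the elastance threshold for their weight would. The article gives no elastance distribution, and at 80 kg with E = 25, or 70 kg with E = 30, there is no excess. The protocol also expects elastance to rise during a manoeuvre, which lowers the volume.
- **That the PEEP chosen in the intervention arm is distorted.** Nothing in the article requires elastance to be measured at the tidal volume used for ventilation, and nothing shows that the PEEP of minimum elastance would move.

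The arms differ in their exposure to manoeuvres by design. That difference is the intervention and not a fault of this wording.

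**Conclusion.** The contradiction is real and confined to less stiff lungs. There, the RM_Max and SRM steps deliver more than the 8 ml/kg stated for all manoeuvres once elastance is below about 32 (58 kg), 27 (70 kg) or 23 cmH2O/L (80 kg). The size depends on weight and on an elastance that must be assumed, and some combinations show no excess. These figures rest on the single-compartment relation with full equilibration.

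How many patients would be affected cannot be worked out from the article. The excess lasts only for the manoeuvre and, where it occurs, would fall mainly on the intervention arm. The error in the worked example is minor: no eligibility or analysis step uses it. The point is worth correcting before recruitment, but it does not threaten the primary comparison on what the document shows.

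**What to change.** Reconcile the general text in *Recruitment manoeuvres (RM)*, the description and steps of *RM_Max; MBV*, the *PUMP* section and the steps of *Standard practice SRM*. Each manoeuvre should have one rule for inspiratory pressure that says which quantity, tidal volume or driving pressure, governs while it is running and which is only a ceiling. The rule should cover lungs that are less stiff as well as those that are stiff. Which rule applies is for the investigators to decide.

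Check that the software-guided steps match the reconciled text. The software is not shown, so nothing here says that it is misaligned.

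Correct the worked example so that its elastance, weight and volume agree. At 15 cmH2O and 58 kg, volume falls below 6 ml/kg only above about 43 cmH2O/L; at 40 it is 375 ml, or 6.5 ml/kg.

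The cost is protocol and bedside-instruction wording plus the software check. No extra patients, measurements or procedures are needed.

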### RM checklist

Before performing any RM, the following criteria are considered. Any RM must be delayed until these conditions are corrected in the consideration of the following at-risk patient conditions:
Haemodynamic instability (e.g. ongoing haemorrhage).Not optimally resuscitated with fluids (e.g. stable blood pressure, but pulse pressure variation ≥ 12% because of inadequate left ventricular preload)? This is only applicable in the absence of spontaneous breathing.Evidence of barotrauma since enrolment?
If there is new barotrauma, RMs must not be attempted and the participant will be withdrawn from trial. They will continue to be observed and followed up. A SAE will be reported.

### RM preparation steps

Once the RM checklist conditions are met, the patient can be prepared for a RM by ensuring:
There is a reliable arterial line.The patient is supine, 15–30° head up.The endotracheal tube (ETT) cuff is inflated to 45 cmH_2_O (RM_Max_ or SRM) or 35–40 cmH_2_O (PUMP) to ensure there is no leak at maximum airway pressures. The ETT cuff is deflated to less than 30 cmH_2_O at the end of the RM procedures.The peak pressure alarm is set to 45 cmH_2_O (RM_Max_, PUMP, SRM)SpO_2_ is in the target range (FiO_2_ < 60%: 93–95% or FiO_2_ ≥ 60%: 90–92%), and ABGs have been recorded within the last 60 min.If the patient is not on vasoactive drugs, intravenous (i.v.) adrenaline (or other suitable vasoactive drug) is available in the event of hypotension.

### RM termination

RMs should be terminated if at any time during the RM any of the following changes persist for more than 3 min:
Desaturation, with SpO_2_ < 88%.New bradycardia (heart rate < 60 beats per minute) or,New tachycardia (heart > 140 beats per minute) or,New arrhythmia leading to new bradycardia (2) or new tachycardia (3) or,New hypotension (reduction in MAP by 40% or MAP < 60 mmHg).

This RM termination criteria applies to all RM procedures in both arms.

### RM_Max_; MBV

The RM_Max_ is a computer-guided staircase RM procedure in the MBV intervention arm. This method is designed to safely increase the inspiratory pressure to a maximum airway pressure of 40–43 cmH_2_O, with DP limited to 15 cmH_2_O, and maximum PEEP limited to 25–28 cmH_2_O. The RM_Max_ is guided by the CURE software using a validated model-based method, which estimates elastance to determine the optimal PEEP [23, 31].

The RM_Max_ is carried out by intensive care specialists or senior trainees familiar with this technique. This procedure is only carried out during working hours (0800–1800 hours), but preferably within 4–6 h of enrolment. However, for patients enrolled overnight, unless there are compelling reasons to carry out an RM_Max_, this procedure may be delayed till the following morning (0800 hours).

Contra-indicated preconditions to an RM_Max_ are excluded using the RM checklist. If it is safe to proceed, the patient is prepared for the RM_Max_.

The following instructions are given to the clinician:
Adjust oxygenation to meet the target range.Titrate sedation so the patient is not verbally responsive and has loss of their eyelash reflex. Use fentanyl or morphine increments with propofol to provide a “balanced” deeper sedation level. Give rocuronium 1.0–1.5 mg/kg through a reliable i.v. line; ensure the line is flushed.Set the ventilator to SIMV-PC (pressure control) mode.Set peak inspiratory pressure (Pi) to 15 cmH_2_O above PEEP.Ensure the initial PEEP is ≤ 15 cmH_2_O.Start maximum recruitment on the CURE soft programme.Follow the steps of the CURE soft protocol: during the RM_Max_, increase PEEP in steps of 4 cmH_2_O above the baseline PEEP level until Pi reaches 40–43 cmH_2_O or PEEP 25–28 cmH_2_O. Then reduce PEEP in 4 cmH_2_O decrements until the original starting PEEP is reached. Adjust FiO_2_ throughout the procedure to keep SpO_2_ ≥ 90%.Once PEEP has been returned to the initial setting, perform a second RM_max_ using the same method in point 7. The RM_Max_ is carried out twice. During the first RM_Max_ the elastance changes in PEEP level are more variable and therefore less predictable. The non-recruited lung is highly heterogeneous with regions of collapse and consolidation. The first RM_Max_ is used to recruit these de-recruited regions. The second manoeuvre is used to estimate optimal PEEP from repeated estimates of elastance changes during decremental PEEP titration.The CURE soft programme will recommend an optimal PEEP at the end of the second RM_Max_. You may either accept this computerised recommendation, or reject it (with a reason) if you feel the new PEEP level is inappropriate. If rejected, record your reason(s) on the programme.Return the patient to the previous ventilation mode.Adjust V_T_ to ≤ 6–8 ml/kg IBW. If the plateau pressure is > 30 cmH_2_O, adjust the V_T_ down to 4–6 ml/kg IBW and tolerate permissive hypercapnia. Also ensure that the DP remains at ≤ 15 cmH_2_O. You may increase the respiratory rate up to 30 breaths/min provided there is no significant auto-PEEP causing breath stacking.Reduce the ETT cuff pressure to the previous level and re-set ventilator alarms to previous settings.Record ABGs 30–60 mins after conclusion of the procedure.

### Repeating the RM_Max_

The RM_Max_ may be repeated only when the following conditions are met:
If there is a significant change in the participant’s condition, e.g. new severe hypoxaemia (SpO_2_ < 90% and FiO_2_ ≥ 60%; P/F ~ 100) andPatient conditions for which lung recruitment is contraindicated are excluded (e.g. endobronchial intubation, mucous plugging, pneumothorax etc) andAnalgesia and sedation and patient position have been optimised (consider small changes to respiratory rate, V_T_ and pressure support, or a rocuronium infusion) andThe PUMP fails to improve oxygenation

